### Settings

Three homeless outreach services in Lothian, Scotland, and three hostels in Liverpool and Bradford, England, were chosen for implementation of this intervention. All hosting services are non-profit, third sector housing organisations. To enable assessment of the differences between intervention and non-intervention care pathways, we have identified two standard care settings that are similar to the intervention sites, e.g. third sector/type of funding/types of staff roles and numbers in place/aims of service. Whether the settings are comparable will be explored in the process evaluation. As non-statutory, third sector services, developed to meet the needs of their specific populations, it will be highly unlikely that any service is completely comparable. In the two standard care sites, the same health check measures will be used with a sample of residents/service users in order to assess population differences and the acceptability of use of measures outside of the context of our intervention. We will also undertake non-participant observation in both intervention and standard care sites to document similarities/differences between care pathways. Interrogating the role of context will be key to our understanding of how the intervention works, most specifically in terms of the role of each of the services in hosting the Peer Navigators and the study and particular facilitators and barriers to the intervention.

### Recruitment and eligibility assessment

Recruitment to the intervention will be an ongoing process until the desired sample size of 60 participants is reached (see below for a discussion on sample size), or until the mid April 2019 (combining two trial recruitment strategies identified by Thoma et al. [82]). As described in the feasibility study conducted by Ferguson and Xie, for each participant that leaves the study, a new participant will be invited to engage in the intervention [83] until the ‘cutoff’ point of mid April 2019. In the event that there are more than 60 people who wish to take part, a waiting list will be kept so that if a participant drops out, a new person can be engaged until the ‘cutoff’ date.

To be eligible, participants must be currently homeless or at risk of homelessness, over the age of 18 years, self-report alcohol or drug problems (with participants themselves recognising that their substance use is a problem for them, prompted by questions such as ‘do you use alcohol or drugs? do you see this as a problem for you?’) and able to provide informed consent. The Peer Navigators will identify participants through the service in which they work, and from the outreach activities that they engage in, and from other referral points such as healthcare professionals and other agencies working in the local environment. A collaborative process will take place, to discuss the eligibility of each participant who is approached, between the Peer Navigator and the Service Managers in each of the study settings who line manage the Peer Navigator, in partnership with the study Chief Investigator and the study team.

Two Peer Navigators are based in three homelessness outreach services in Scotland and two are based in three hostels (Lifehouses) in the north of England. Two standard care sites have been selected, one in Scotland (third sector outreach service run by one of the providers of the intervention sites serving clients with similar needs) and one in England (third sector hostel run by one of the providers of the intervention sites serving clients with similar needs), that are comparable to the intervention sites in key ways (e.g. the needs of the client base, geographical area, staffing levels, organisational ethos and culture) but will not have a Peer Navigator located within them.

### Consent

All identified eligible intervention participants in the study intervention settings will be approached by the Peer Navigators and provided with a Participant Information Sheet and then asked to provide written informed consent at least 48 h later if they wish to join the intervention. Participants are advised that they might be approached at a later point regarding participating in the associated qualitative data collection (interviews) element of the study. This will be a separate process of providing information and then gaining informed consent; only a sub-set will be involved in this aspect of the study. These interviews will be conducted by Peer Researchers, who have been recruited and trained by the Scottish Drugs Forum (SDF). These individuals are separate from, and unknown to, the Peer Navigators. The Peer Researchers will have lived experience of problem substance use and will receive training in research methods, the study methods and the intervention. Interviews will also be conducted with staff in the intervention and standard care sites and with the Peer Navigators. (Examples of the Participant Information Sheets and consent forms are provided as Additional files 2 and 3).

Participants will be asked to state that they accept and understand limitations to confidentiality within the qualitative interviews and/or support discussions with Peer Navigators. These limitations refer to information about knowledge of harm or abuse to someone including the participant. If such disclosures do occur, this information will be shared with senior members of staff in each setting who will conduct a risk assessment as per their duty of care. In the event of this situation occurring, the person taking the disclosure will call the Chief Investigator, with an adverse event form being completed.

### Sampling, sample size and data collection

As this is a feasibility and acceptability study, no formal power calculation is required [84]. We aim to recruit 60 people to the intervention. This sample size was determined on the basis that, although sample sizes of between 30 and 50 have been recommended for feasibility studies [85, 86], we expect a degree of attrition because of the unstable nature of participants’ lives. In consultation with clinical colleagues, we slightly inflated our sample size based on the likelihood of 10–15% attrition to ensure participant volume [82]. While this sample is deemed a manageable caseload for the Peer Navigators, this will be carefully assessed as part of the process evaluation.

There are a number of different samples for data collection within the process evaluation:All consenting intervention participants (*n* = 60) will have quantitative data collected through the holistic health checksA purposive sub-sample (*n* = 20–25) of intervention participants will be asked to participate in semi-structured interviews (conducted by Peer Researchers), ideally at two time points if available/willingParticipants who leave the study will be asked to complete a short questionnaire provided by Service Managers, which covers some key questions about their experiences in working with the Peer NavigatorAll four Peer Navigators (using criterion sampling) will participate in semi-structured interviews at three time pointsService staff in both intervention and standard care settings (*n* = 16) will be identified using purposive sampling and asked to participate in semi-structured interviews

The purposive approach to sampling of the intervention participants for qualitative interviews will take account of the diversity of settings, gender, age, race/ethnicity, and the presence of disability or significant health concern, alcohol or drug use as main problem substance.

A small number of Peer Researchers will conduct qualitative semi-structured interviews with the sub-sample of intervention participants to examine their views on the intervention. Our team believes that participants in the intervention will be more comfortable speaking with someone who has been through similar life experiences and that this will lead to ‘richer’, more ‘valid’ data being gathered in relation to participant experiences of the intervention [87]. The Peer Researchers will be qualified partly on the basis of the lived experience of problem substance use and/or homelessness. They will be recruited by SDF from their wider pool of Peer Researchers, and although trained in research methods, they will be further trained in the SHARPS study methods and intervention. They will be actively supported by a User Involvement Officer from SDF on site during interviews. Interviews will take place where participants are willing/available at two time points, in the early to middle phase (January–April 2019) and then towards the end of the intervention (August–September 2019), to explore whether perceptions change over time.

Research team members will identify and recruit the wider service staff (*n* = 16) and participant (*n* = 20–25) samples at each of the six intervention sites and two standard care sites. The research team members will conduct all staff interviews. Staff samples will be purposive, based on diversity of setting, role within service, disciplinary background, gender and age. Qualitative interviews will be undertaken with all four Peer Navigators at three time points (beginning—June 2019, middle—April 2019 and end—November 2019) by research team members to assess changes in perception and practice. Please see Table 1 for more details on sampling, recruitment and data collection.

**Table 1 Tab1:** Sampling, recruitment and data collection strategy

Sample	Recruitment strategy and timescale	Data collection methods and proposed sample size
1. Participants receiving the intervention	People who are homeless with problem substance use who are engaged with the intervention A sub-group of those in the intervention will be identified by researchers as the process evaluation sample for qualitative data collection. Timescale: months 9–11 and 16–17	As part of the holistic health check (*n* = 60), standardised measures of socio-demographic characteristics, housing status/quality and general health status; quality of life (SF36); substance use (SURE and MAP); mental health (GAD7 and PHQ9); will be used, plus measures to assess relationship quality (CARE). All participants will have this information collected if they consent to the health checks and the data collection component. The health checks will be conducted twice, towards the start and near the end of the intervention, by researchers. Individual face-to-face interviews (*n* = 20–25) conducted on two occasions by Peer Researchers approximately 20–40 min in duration. Interviews will examine various elements of feasibility and acceptability of intervention (except in Liverpool where only one interview will be attempted due to shortened intervention).
2. Participants who have dropped out	People who are homeless with problem substance use who initially engage but leave the intervention early, identified by the Service Manager and invited to complete a short, structured questionnaire. Timescale: as soon as possible after ending engagement.	All participants who drop out will be provided (via the Service Manager where the Peer Navigator is based) with a short questionnaire to voluntarily complete and return via a sealed envelope. This will ask questions about their experiences of working with the Peer Navigator and the reasons underlying their decision to withdraw their participation. This will not be shared with the Peer Navigator but go directly to the study Chief Investigator.
3. Peer Navigators	All four Peer Navigators employed for the duration of the project (training/intervention development, mid-intervention delivery and towards the end of the intervention period).	Individual interviews (*n* = 4) at three time points conducted by researchers (approx. 60–90 min). Interviews examine recruitment, health checks and potential outcome measures, training and support/supervision, fit to context, fidelity, acceptability—topics informed by feasibility study literature [73].
4. Service staff in intervention and standard care settings	Support workers, team leaders, managers/other staff working in the six intervention sites and two standard care settings. Timescale: months 6–12	Interviews (*n* = 16 across intervention/standard care sites), conducted by researchers (approx. 60 min) examining issues listed in box above, drawing on feasibility study literature on areas of focus noted above [73].
5. Intervention/standard care settings	Six intervention sites and two standard care sites will be included Timescale: months 6–12	Semi-structured, non-participant observations in all sites to gain an understanding of the of the culture and context of the settings, staffing levels, client group, activities provided, and fit between intervention and setting in the intervention sites.

### Intervention and intervention guide/manual

Another important dimension of this study is the co-production of the intervention at the start of the study. The intervention and intervention guide/manual will be co-produced by experts in homelessness, inclusion health, and PIEs and relational interventions; representatives from homelessness and third sector organisations; peers and people who have experienced homelessness and/or problem substance use via our Experts by Experience group and the Peer Navigators; and relevant health/medical professionals, following INVOLVE guidance [88]. We will do this by convening a full-day meeting to discuss the key components of the intervention and how these will be implemented. During this meeting, we will plan for the intervention end point in a way that is sensitive to the fact that participants who engage will have experienced many other relationship losses. We will aim to ensure that participants are connected to other support agencies before the intervention ends.

Following this full-day meeting, the study team will develop draft versions of the intervention and training manuals for circulation to all parties. We will work closely with all organisations and individuals, including the Peer Navigators, to ensure that these documents meet the needs of the target group, drawing on current literature and stakeholders’ own experience of working in the field and/or accessing services as a service user. The intervention manual will provide the Peer Navigators with the necessary information to carry out their roles, with detailed information about particular concepts and approaches; health and social issues affecting participants; study information; the intervention; and key contacts and local information. Service-based line managers of the Peer Navigators will also receive their own copies for reference. In line with other relationship-based therapies, manualisation of the intervention will be flexible rather than completely structured, as rigid approaches can reduce effectiveness, but will include instruction on PIEs, health check/measures and referral pathways. The manual/guidance will be further refined post-intervention and evaluation as one of the study outputs.

Four part-time (30 h per week, 18-month contracts) Peer Navigators will be employed by the lead partner agency, paid on a Specialist Support Worker rate, and have the same terms and conditions as other staff in the organisation, including the right to continuing professional development as part of their roles. The Peer Navigators will provide a non-judgemental relationship and practical and emotional support for each recruited participant for a period of between 2 and 12 months, depending on the setting. The support provided will consist of support regarding the reduction of harms/potential for accessing treatment related to a person’s substance use, physical and mental health, housing, relationships with family, developing skills and hobbies, and training and education. The Peer Navigators will work with participants to identify these support needs and to put in place referrals, support to attend appointments, support to build relationships with new services and so on. As part of the proposal development work, the importance of practical support to attend appointments was highlighted by our experts by experience advisers consulted as part of the proposal development. In order to provide participants with this practical support, the Peer Navigators will have access to small amounts of petty cash held in the service settings. Support will be offered for up to 12 months (2–12 months depending on the setting), and not withdrawn on the basis of continued problem substance use or abstinence. Towards the end of the intervention, the Peer Navigators will have a conversation with participants to identify an ‘exit strategy’ in terms of their support needs in the months until and after the end of the intervention. Figure 2 shows the study flowchart.

**Fig. 2 Fig2:**
[figure not shown]
SHARPS study flowchart

**Fig. 3 Fig3:**
[figure not shown]
SHARPS study detailed timeline

### Training in the intervention and fidelity

The Peer Navigators will receive induction and advanced ‘front loaded’ training in the first 3 months in their post and will receive updates as appropriate throughout the study. Training will be in areas related to the intervention such as harm reduction, the relevance of a trauma to substance use behaviour, professional boundaries and therapeutic relationships, and PIEs. They will also receive training and induction to the study, including on recruitment and relevant ethical issues such as assessing eligibility and informed consent. A training manual will be produced and refined as part of the study. Fidelity to the guide and core components of the intervention will be assessed in the interviews with Peer Navigators. It is important to formally acknowledge that the study team understands that each Peer Navigator will bring their own experiences and individuality to the intervention and to each of their relationships with participants and the feasibility design allows a diversity of approach to be well explored and reflected upon. Each Peer Navigator will receive regular one-to-one (face-to-face or phone) clinical supervision with a Clinical Psychologist with expertise in working with the participant group and supporting staff working with this group. The value of this supervision will be explored in the process evaluation.

### Outcome measures via ‘holistic health checks’

The following outcome measures will be administered as two ‘holistic health checks’, one in the first few months of the intervention (November 2018–May 2019) and one near the end (August–October 2019).Socio-demographic characteristics, housing status/quality and general health status will be assessed and cover demographics, education, housing, health conditions, medication, health status and future service use.Mental health will be measured using the Generalised Anxiety Disorder 7 (GAD7), a 7-item tool covering symptoms of anxiety [89], and the Patient Health Questionnaire 9 (PHQ9), a 9-item tool covering symptoms of depression [90].Substance use will be measured using the Maudsley Addiction Profile (MAP), which has been slightly amended to fit the current population (it will not be scored). The 36-item tool covers substance use (type/frequency/method), overdose, treatment, injecting and sexual behaviour, physical and psychological health, social functioning, relationships and illegal activities [91]; and the Substance Use Recovery Evaluator (SURE), a 26-item tool covering drinking and drug use, self-care, relationships, material resources, outlook on life and importance of previous items [92].Health-related quality of life will be measured using the Short-Form 36 (SF36), a 36-item tool covering physical and emotional health status, the effect of health on daily activities and social activities and experiences of pain [93].The quality of the relationship between the Peer Navigator and the participant will be measured using the CARE Patient Feedback Measure, a 10-item tool assessing empathy in the context of relationship [94].

These holistic health checks will take place in a private space with the researchers taking sufficient time to work through each of the measures with each participant allowing time for full discussion if needed. The measures will be paper-based and conducted in a sensitive and relational manner. The Peer Navigators will be available throughout if the participant wishes to have their support.

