**Methods:**

A mixed-method feasibility study with concurrent process evaluation will be conducted to explore the feasibility and acceptability of a peer-delivered, relational intervention for people with problem substance use who are homeless. Peer Navigators will be based in homelessness outreach and residential services in Scotland and England. Peer Navigators will work with a small number of participants for up to 12 months providing both practical and emotional support. The sample size for the intervention is 60. Those receiving the intervention must be currently homeless or at risk of homelessness, over the age of 18 years and self-report alcohol/drug problems. A holistic health check will be conducted in the first few months of the intervention and repeated towards the end. Health checks will be conducted by a researcher in the service where the Peer Navigator is based. Semi-structured qualitative interviews with intervention participants and staff in both intervention and standard care settings, and all Peer Navigators, will be conducted to explore their experiences with the intervention. Non-participant observation will be conducted in intervention and standard care sites to document similarities and differences between care pathways.

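### CARE, the participant's rating of the Peer Navigator relationship, may be completed with that Peer Navigator in the room, and the protocol makes no exception for it and does not record presence

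*Protocol article*

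**What the plan says.** The protocol article, under the heading on outcome measures via holistic health checks, lists CARE among the measures given at both checks: "The quality of the relationship between the Peer Navigator and the participant will be measured using the CARE Patient Feedback Measure". It is a 10-item tool about empathy, so the Peer Navigator is the person rated.

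The same section describes the setting: "These holistic health checks will take place in a private space with the researchers taking sufficient time to work through each of the measures". It then adds: "The Peer Navigators will be available throughout if the participant wishes to have their support". The Methods paragraph of the abstract gives the place: "Health checks will be conducted by a researcher in the service where the Peer Navigator is based". The article does not set CARE apart from the other measures on this point, and does not say that the Peer Navigator's presence will be written down.

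Two other sources of feedback are handled differently. In Table 1, participants who drop out return a short questionnaire in a sealed envelope: "This will not be shared with the Peer Navigator but go directly to the study Chief Investigator". Under Consent, the Peer Researchers who interview a sub-set of participants are described so: "These individuals are separate from, and unknown to, the Peer Navigators".

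The Discussion counts the suitability of the outcome measures and good participant experience among the marks of success. One research question asks which outcome measures would suit a full RCT.

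**The concern.** The article places the relationship at the centre of the intervention, and CARE is the one listed number that describes it. The rule on Peer Navigator support covers the whole session, so it also covers the form on which the participant judges that Peer Navigator. The participant still relies on this person for practical and emotional support, which is a plain reason to be reluctant to criticise in front of them.

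Two things are at stake. CARE scores may be shifted in the favourable direction. And the study may misjudge how CARE behaves in this population, for example whether ratings bunch at the top because relationships are good or because of how the form was completed. A later RCT team would inherit that judgement.

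**Working it through.** **1. Is there a figure to reproduce?** None for CARE. The article gives no mean, standard deviation, threshold or number of respondents for it. The point does not depend on the sample size of 60.

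**2. Does the support rule reach CARE?** Set the statements side by side:

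- CARE is one of the measures in both checks.
- Researchers work through each measure with the participant in one session.
- The Peer Navigator is available for all of that session if wanted.
- No measure is excepted.

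So the rating may be given in front of the person rated. This is what the stated rule permits; it is not only a missing detail.

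**3. How is other feedback on the Peer Navigator protected?**

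| Source | Who gives it | Stated protection |
|---|---|---|
| Drop-out questionnaire (Table 1) | Leavers | Sealed; withheld from the Peer Navigator |
| Interviews (Consent; Table 1) | 20–25 intervention participants | Interviewers unknown to the Peer Navigators |
| CARE (outcome measures section) | All consenting intervention participants | Private space and a researcher, but the Peer Navigator may be there on request |

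The interviews cover 20/60 = 33% to 25/60 = 42% of the target sample. For the other 35 to 40 participants, CARE is the main structured feedback on the relationship unless they drop out and return the questionnaire.

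**4. Size of a shift in the mean.** Let *p* be the share of participants with the Peer Navigator present for CARE, and *d* the average rise in their total caused by that presence. Then

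shift in mean = *p* × *d*.

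Neither is in the document. Purely as an assumption, take *p* from 25% to 100% and *d* from 1 to 5 points. The shift then runs from 0.25 × 1 = 0.25 points to 1 × 5 = 5 points. That is a twenty-fold range (5/0.25 = 20) that comes entirely from the assumed inputs. The document therefore fixes no size.

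**5. Could the effect be removed in analysis?** Let *m1* be the mean rating that participants who ask for the Peer Navigator would give privately, and *m0* the same for those who do not ask. The observed difference between the groups would be

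(*m1* − *m0*) + *d*.

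Even with presence recorded, one observed difference cannot separate the two terms. With presence unrecorded, the difference itself cannot be seen. Completing CARE without the Peer Navigator sets *d* to zero by design, and no adjustment is then needed.

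**The case against.** The other side has real force, and it limits the point.

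- **Available is not present.** The default is a participant and a researcher in a private space, and the Peer Navigator joins only at the participant's wish. A reader might infer that CARE is routinely answered in front of the Peer Navigator. The article does not say so.
- **Poor ratings can still appear.** A reader might infer that CARE is unable to reveal a bad relationship. That does not follow, because a participant on bad terms with the Peer Navigator need not invite them.
- **Current participants do have a protected channel.** A reader might infer that only leavers are shielded. The interviews by Peer Researchers contradict this, and the article combines them with the quantitative data.
- **The envelope contrast is imperfect.** The leavers' form passes through the Service Manager, who line-manages the Peer Navigator. CARE goes to a researcher, and nothing says that the Peer Navigator sees it afterwards.
- **No inference rests on CARE.** The analysis is descriptive, the study is non-randomised and no threshold is attached to the score.
- **The support is deliberate.** It is offered to a vulnerable group. The same session includes MAP, with sensitive items, and a reader might want the Peer Navigator out for those too. MAP will not be scored, and a trusted supporter could help or hinder disclosure; the document does not say which.
- **Detail may sit elsewhere.** The intervention manual, not shown, is to cover the health check and its measures.

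What stands is narrower. The article states a rule for the whole session without excepting the one form that rates the person offered as support. Descriptive analysis does not remove a shift in the scores being described, and the interviews reach fewer than half of the target sample.

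**Conclusion.** The point holds as a modest, inexpensive improvement. CARE may be completed with the rated Peer Navigator present, with no stated exception and no record of presence. Ratings given that way are liable to be inflated, and presence is confounded with relationship quality. This weakens the evidence on whether CARE suits a full RCT.

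The upward direction is an expectation from reluctance to criticise someone present; the document neither shows nor measures it. The size is unknown, and any figure would rest on an assumed attendance share and an assumed presence effect. The conclusion also assumes that no unseen manual already takes the Peer Navigator out of the room for CARE. If one does, the article needs only a sentence saying so.

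**What to change.** Add to the health check procedure:

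1. CARE is completed without the Peer Navigator in the room, by the participant alone or with the researcher only.
2. Participants are told beforehand that the Peer Navigator will not see their CARE answers.
3. The form records whether the Peer Navigator was present for any other measure.

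Support during the remaining measures, MAP included, stays at the participant's wish. The cost is a short addition to the procedure and one item on the form. The downside is that a participant who wants the Peer Navigator there goes without that support for 10 items. Presence should be noted at the time, since it cannot be reliably recovered later.
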